### The intervention

Arm 2 and Arm 3 interventions are designed based on the framework that can eventually lead to a self-learning ecosystem in the community to improve early PSE and health outcomes for first-time families.

In Arm 2, we interact with the participants virtually. The participants in this intervention arm will receive weekly mobile messages on important information related to antenatal care, breastfeeding, infant care, child growth and development, and postpartum care. These messages are targeted and time specific according to stages in the pregnancy and early childhood. There were designed by the study team’s health experts as reference to the Ready4K text messaging programme [31], serving as nudges to influence behaviour and guide first-time families in their pregnancy and early parenting journey. In order to create an interactive and sharing environment with peer support, participants are enrolled automatically to a private social media platform group, where they are encouraged to share information, post photos and interact with each other. More detailed and updated health information related to maternity care and parenting skills are available in the social media platform to provide guidance and support to the participants, as well as to encourage self-learning. Meanwhile, participants can post any query on health concern in their first 1000 days, which will be addressed by the study team’s experts. This is a restricted and by-invitation-only social media forum. The contents are monitored by the research staff to ensure this sharing platform contains trustworthy information. We envision that motivated participants will be empowered and eventually, emerge as chat group leaders in this platform.

In Arm 3, we conduct midwife-led continuity care involving individual teleconferencing sessions. Participants will be encountered by midwives who interact with them at various time points throughout the study. During pregnancy, one session that lasts for 15–20 min is held in the antenatal clinic per trimester. Any questions pertaining to pregnancy or childbirth can be clarified with the midwife. During post-delivery, the same midwife will conduct individualised teleconferencing sessions at 1- and 2-week postpartum, and call to check for progression at 6-week, 3- and 6-month postpartum. Participants can discuss any concern relating to postpartum health, infant care, breastfeeding, child growth and development with the midwife. In the case when there is uncertainty about queries asked by the participant, advice from the study team’s health experts will be sought. We envision that motivated participants will be empowered and eventually, emerge as support volunteers assisting in midwifery care delivery in the community.

### Outcome measures

We quantify the impact of interventions by measuring PSE in first-time mothers, along with specific health outcomes.

#### Primary outcome

The primary outcome of this RCT is PSE, measured using the Tool to measure Parenting Self-Efficacy (TOPSE) and the Parental Sense of Competence Scale (PSOC) at 6-week as the primary endpoint, followed by 6-, 12-, 18- and 24-month post-delivery. We include both TOPSE and PSOC, as the combination use of these two tools provides a comprehensive measure on the domain-specific and domain-general self-efficacy components. In addition, we are able to evaluate, following suggestions by Bandura [36], any differences in employing two assessment strategies operating at different levels of specificity [8].

The TOPSE is a multidimensional, self-report measure designed to assess parents’ perceived ability to parent their children, which took into account the views and experience of parents from a range of cultural and social backgrounds [37, 38]. The theoretical underpinning of TOPSE is based on self-efficacy theory developed by Bandura [36, 39]. It consists of 48 items which are divided into eight subsections: (1) emotion and affection, (2) play and enjoyment, (3) empathy and understanding, (4) control, (5) discipline and setting boundaries, (6) pressures, (7) self-acceptance and (8) learning and knowledge. Participants will be requested to rate items using a 11-point Likert scale ranging from 0 (completely disagree) to 10 (completely agree). The higher the score, the higher the level of PSE.

The PSOC is a self-report instrument designed to measure parenting satisfaction and efficacy [40]. It is a domain-general measure with items describing common parental ideas regardless of the child’s age and the specific tasks that the parent has to face [40]. Although the PSOC has mainly been used in parents with children, it has been found to be valid for use in parents with infants [41, 42]. It consists of 17 items scored on a 6-point Likert scale ranging from 1 (strongly disagree) to 6 (strongly agree). The higher the score, the higher the level of parenting satisfaction and self-efficacy.

#### Secondary outcomes

Secondary outcomes include health and birth experience, mental wellness and nutritional outcomes, assessed using validated patient reported outcome measurements, including the use of the International Consortium for Health Outcomes Measurement (ICHOM) Standard Set of Outcome Measures for Pregnancy and Childbirth [43] and by anthropometric measures. Time points of assessment and ICHOM tools are indicated in Table 1.

Health experience will be assessed using the Patient Reported Outcomes Measurement Information System (PROMIS) Global-10 [44]. The instrument consists of 10 items representing general health, physical health, mental health, social health, pain, fatigue, and overall perceived quality of life. Nine of the 10 items are scored on a 5-point Likert scale ranging from 1 (poor/not at all) to 5 (excellent/completely). The pain – 10th item, is scored from 0 (no pain) to 10 (worst imaginable pain). This instrument has been found valid to be used for maternity population [45].

Birth experience will be assessed using the Birth Satisfaction Scale-Revised [46]. The instrument measures women’s perceptions on quality of care provision, women’s personal attributes and stress experienced during labour. It consists of 10 items rated on a 5-point Likert scale ranging from 0 (strongly disagree) to 4 (strongly agree).

Mental wellness will be assessed using the Patient Health Questionnaire-2 (PHQ-2) and the Edinburg Postnatal Depression Scale (EPDS). The PHQ-2 consists of 2 items rated on a 4-point Likert scale from 0 (not all all) to 3 (nearly every day), to screen for depression as a first step approach [47]. EPDS will be used when a woman scores a three or above on the PHQ-2, in order to further assess depressive symptoms in details. Although EPDS was originally designed to measure postnatal depression [48], it has been shown to be valid in assessing antenatal depression [49]. It consists of 10 items rated on a 4-point Likert scale, ranging from 0 (as much as I always could) to 3 (not at all).

Nutritional outcomes are assessed based on breastfeeding and infant feeding practices, as well as anthropometric measures. We evaluate breastfeeding in terms of breastfeeding success, breastfeeding confidence and breastfeeding self-efficacy. Breastfeeding success is measured according to feeding mode in the past 7 days, with options of ‘only breast milk’, ‘combination of breast milk, formula and/or water’, and ‘only formula, water or other liquids but not breast milk’ [50]. Breastfeeding confidence is evaluated based on a 5-point Likert scale from 1 (not at all) to 5 (very confident) [50]. Breastfeeding Self-Efficacy Score-Short Form is used to assess maternal confidence in her ability to breastfeed her new baby [51]. The instrument consists of 14 items rated on a 5-point Likert scale, ranging from 1 (not at all) to 5 (very confident). The Infant Feeding Questionnaire (IFQ) is used to assess maternal feeding beliefs and practices [52]. This tool has been shown to be valid for use in our population [53]. IFQ is a 28-item questionnaire rated on a 5-point Likert scale, ranging from 1 (never/disagree a lot) to 5 (always/agree a lot). Nutritional status for both mother and child is assessed throughout the study period, by evaluating maternal weight status across pregnancy and during postpartum, and child growth over the first 2 years, i.e. weight and length.

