### Aims

The main goal of the Community-enabled Readiness for first 1000 Days Learning Ecosystem (CRADLE) study is to promote and sustain healthy behaviour both for the mother and offspring in the first 1000 days and beyond, through a supportive community-led sharing environment for first-time families. To achieve the goal, we developed a virtual interactive and sharing platform, integrated with choice architecture using calibrated nudges, along with midwife-led care service. Our target is to create a self-learning ecosystem by providing knowledge support and guidance, via interactions with health care professionals and peer learning through e-platform. This will in turn create opportunities for the participants to become empowered and eventually develop as community volunteers for maternity care.

Specifically, we aim to examine the effects on PSE and health outcomes in mother and child, with the use of behavioural nudges in the form of text messages (a choice architecture technique) and midwife-led care service, from pregnancy until the first 2 years post-delivery. We hypothesise that during the first 1000 days, the use of virtual nudging tool in the form of text messages supplemented with social media, or physical care from midwives supplemented with individualised teleconferencing sessions will lead to a better maternal PSE, health and birth experience, mental wellness, and nutritional outcomes in both mother-child, compared with those who are receiving standard routine care. The framework of the study is shown in Fig. 1.

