## Methods/design

### Trial design

CRADLE is conceptualised as a three-arm, parallel-group, non-blinded randomised control trial (RCT). The allocation ratio of the control group to two intervention groups is 1:1:1. The three arms comprise: (1) standard routine care; (2) behavioural nudges (text messages) along with the use of a social media platform; (3) midwife-led continuity care involving individualised teleconferencing sessions. The protocol has followed the SPIRIT guidelines (see Additional file 1). The trial registration number of the study is ClinicalTrials.gov NCT04275765.

The flow of the trial is shown in Fig. 2. Following informed consent at the recruitment visit, a baseline assessment on maternal sociodemographic characteristics and health status will be conducted, followed by randomisation to the control or intervention group (Arm 2 or 3) using the electronic randomisation list. Depending on the follow-up time-point (i.e. 30-week, at birth, 6-week, 6-, 12-, 18-, and 24-month post-delivery), every participant is required to complete few sets of online questionnaires for assessments on PSE, health and birth experience, mental wellness and feeding practice. A 2-week timeframe is given to the participants to complete the questionnaires, depending on their preferable schedule and availability within the period. Maternal and child anthropometric measures including weight and height are also assessed. Details of study measures and questionnaires used according to the visit time points are presented in Table 1.

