**Mental wellness**								
Patient Health Questionaire-2^*^	√	√		√	√			
Edinburgh Postnatal Depression Scale	√	√		√	√			

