### Statistical analysis

One-way analysis of variance (ANOVA) and chi-square tests or Fisher’s exact tests will be used to compare differences in baseline characteristics among the three arms. The primary analysis will be according to the intention-to-treat principle, i.e. all participants who were assigned to a condition. Differences in outcomes across three arms at each time-point will be compared using the one-way analysis of covariance (ANCOVA) (General Linear Model, GLM), adjusting for baseline characteristics and measures. Bonferroni correction will be performed for pair-wise comparisons. Linear mixed models will be used to compare the outcomes across time points among the three arms, adjusting for baseline characteristics and measures. Additionally, a priori sensitivity analysis will be conducted for complete cases, i.e. participants with complete follow-up and data. There are no formal planned interim analyses of the primary outcome, but progress reports on all data issues will be presented to investigators of the study team. The level of statistical significance will be set at 0.05 (two-tailed) and 95% confidence intervals will be calculated.

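### EPDS is scored only in women with PHQ-2 of 3 or more, so comparing EPDS means between arms after randomisation compares selected subsets if the interventions change PHQ-2

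*Protocol article*

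**What the plan says.** In the protocol article, Secondary outcomes, both scales are named as measures: "Mental wellness will be assessed using the Patient Health Questionnaire-2 (PHQ-2) and the Edinburg Postnatal Depression Scale (EPDS". PHQ-2 is used "to screen for depression as a first step approach", and the second step is conditional: "EPDS will be used when a woman scores a three or above on the PHQ-2, in order to further assess depressive symptoms in details".

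Table 1 (Mental wellness) schedules PHQ-2 and the "Edinburgh Postnatal Depression Scale" at the same four visits: baseline, third trimester, 6 weeks and 6 months. It does not mark EPDS as conditional.

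Trial design puts randomisation after baseline: "a baseline assessment on maternal sociodemographic characteristics and health status will be conducted, followed by randomisation to the control or intervention group". Three of the four PHQ-2 measurements that open the way to EPDS are therefore post-randomisation. Aims hypothesises that the interventions "will lead to a better maternal PSE, health and birth experience, mental wellness, and nutritional outcomes in both mother-child".

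Statistical analysis states: "Differences in outcomes across three arms at each time-point will be compared using the one-way analysis of covariance (ANCOVA) (General Linear Model, GLM", with adjustment for baseline characteristics and measures. The primary analysis follows intention to treat and includes everyone assigned. Nothing exempts EPDS, calls it descriptive, or says how women below the PHQ-2 threshold are counted.

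**The concern.** At each follow-up visit an EPDS score exists only for women who passed a filter measured after randomisation, and the trial expects its interventions to act on what that filter measures. If they do, milder cases in an intervention arm drop below the threshold and leave the EPDS set, while the more severe remain. The women compared on EPDS are then no longer the groups that were randomised, and an intention-to-treat EPDS mean cannot be formed. A real benefit could look smaller, absent or even reversed.

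Adjusting for baseline EPDS adds a separate problem. That score is also conditional, so the model would keep only women positive both at baseline and at the follow-up visit. The baseline filter precedes randomisation, so it adds no bias of its own, but it costs sample size.

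**Working it through.** The documents give no screen-positive rate, EPDS standard deviation, EPDS effect or EPDS power, so there is no stated figure to reproduce. The size below rests on a model with assumed inputs.

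**Inputs from the article.** Threshold PHQ-2 of 3 or more (Secondary outcomes); three post-randomisation visits (Table 1); 250 per arm recruited and 150 per arm required (Sample size); two-sided 5% level (Statistical analysis).

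**Assumed inputs.** Control screen-positive rate p = 5%, 10% or 20%; correlation rho = 0.5 or 0.7. The effect of -0.35 SD borrows the size planned for TOPSE, purely as an illustration. Negative means better.

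**Model.** PHQ-2 and EPDS are standard normal variables with correlation rho, and EPDS is seen only when PHQ-2 exceeds c, where 1 - Phi(c) = p. With intervention effects dP on PHQ-2 and dE on EPDS, the expected EPDS difference among screen-positives is

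dE + rho × [lambda(c - dP) - lambda(c)], where lambda(x) = phi(x) / (1 - Phi(x)).

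**Worked case, p = 10%, dP = dE = -0.35.** c = 1.282 and lambda(c) = 0.1755/0.1000 = 1.755. c - dP = 1.632 and lambda = 0.1054/0.0514 = 2.051. The bracket is 0.296.
- rho = 0.5: -0.35 + 0.148 = -0.202
- rho = 0.7: -0.35 + 0.207 = -0.143

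**All cases (SD units).**

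| Control positive rate | rho | dP = dE = -0.35 | dP = -0.35, dE = -0.175 | dP = -0.5, dE = -0.1 |
|---|---|---|---|---|
| 5% | 0.5 | -0.197 | -0.022 | +0.120 |
| 5% | 0.7 | -0.136 | +0.039 | +0.208 |
| 10% | 0.5 | -0.202 | -0.027 | +0.113 |
| 10% | 0.7 | -0.143 | +0.032 | +0.198 |
| 20% | 0.5 | -0.210 | -0.035 | +0.103 |
| 20% | 0.7 | -0.153 | +0.022 | +0.184 |

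With equal effects on both scales, 40-61% of the effect is hidden but the sign is kept. The sign reverses when EPDS improves sufficiently less than PHQ-2. With dP = 0 the bracket is zero and the expected difference is dE, so there is no selection bias.

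**Benefit in milder cases only.** A simulation of 2,000,000 women (10% positive in controls, correlation 0.64) gave an improvement of 0.5 SD to all but the most severe. The true mean difference was -0.47 SD; the difference among screen-positives was +0.20 SD.

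**How many women have EPDS.** With no PHQ-2 effect, 10-20% of 150 is 15-30 and 10-20% of 250 is 25-50. If PHQ-2 improves by 0.35 SD, the arms become unequal: of 250, about 25 control against 13 intervention at p = 10%, and 50 against 29 at p = 20%.

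**Power.** For a two-sided 5% t-test at d = 0.35: 15% with 15 per arm, 27% with 30, 23% with 25 and 41% with 50. This is before any attenuation or multiplicity correction.

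**With baseline EPDS as covariate.** Assuming a correlation of 0.5 between baseline and follow-up PHQ-2, the share positive at both visits is 3.2%, 5.8% and 8.7% for rates of 10%, 15% and 20%. At 15% that is 0.058 × 150 = about 9 women, or 0.058 × 250 = about 14.

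**The case against.** The article describes a two-step assessment and nowhere names an EPDS mean as an endpoint. The ANCOVA sentence is general; read literally it would also cover the three-category breastfeeding outcome. An analysis plan that is not shown may handle the two-step measure properly, and a valid outcome can be built from the data already collected. This is a fair limit on what can be claimed. It does not remove the point, because the text as it stands names EPDS as an outcome, makes its collection conditional, and sends outcomes to ANCOVA without exception. No later analysis can supply scores that were never collected.

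A reader might infer more than the documents support:

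- **That the EPDS result will be biased or will show harm.** The bias needs an effect on PHQ-2, which the article only hypothesises. Reversal needs more: a weaker effect on EPDS than on PHQ-2, or benefit concentrated in milder cases.
- **That the mental-wellness comparison as a whole is lost.** PHQ-2 is scheduled for all women at the same visits. EPDS is one of two tools in one secondary domain; the primary outcome and the sample size are untouched.
- **That the filter certainly applies visit by visit.** This is inferred from the paired schedule in Table 1; the text does not say it.
- **That only 150 per arm are available.** That number allows for dropout over the full 1000 days, whereas EPDS ends at 6 months. Hence the range up to 250.
- **That baseline EPDS is a named covariate.** The article says only baseline measures.

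A short screen before a longer scale is also a reasonable way to limit burden and identify cases. The difficulty lies in using the second step as a between-arm outcome.

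**Conclusion.** The point holds in limited form, and the plan should be corrected. Followed as written, an EPDS comparison at the third trimester, 6 weeks or 6 months is made in subsets selected after randomisation. It is distorted if the interventions change PHQ-2. Under the assumed inputs, a true -0.35 SD effect on both scales shows as -0.14 to -0.21 SD, and reversal is possible under the further conditions given above. Without an effect on PHQ-2 the comparison is unbiased but rests on roughly 15-50 women per arm, fewer if baseline EPDS is a covariate. The direction of the argument follows from the text; every magnitude depends on assumed rates, correlations and effects. The consequence is confined to one secondary measure.

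**What to change.** 1. Reconcile Table 1 with Secondary outcomes: mark EPDS as conditional, and state whether the PHQ-2 from the same visit decides.
2. State that the between-arm mental-wellness outcomes are those defined for all randomised women: PHQ-2, and a two-step binary outcome (PHQ-2 of 3 or more and EPDS above a cut-off fixed in advance), with PHQ-2-negative women counted as negative.
3. Report EPDS means among screen-positives descriptively only, and do not use the conditional baseline EPDS as a covariate.

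These steps need only wording and use data already being collected.

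The alternative is to send the 10-item EPDS to every woman at its four scheduled visits. That would allow a randomised comparison of EPDS means, but it adds participant burden and needs a protocol amendment, possibly with further consent. Because recruitment began in June 2020, it would also leave mixed collection among women already enrolled.

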### Statistical analysis

One-way analysis of variance (ANOVA) and chi-square tests or Fisher’s exact tests will be used to compare differences in baseline characteristics among the three arms. The primary analysis will be according to the intention-to-treat principle, i.e. all participants who were assigned to a condition. Differences in outcomes across three arms at each time-point will be compared using the one-way analysis of covariance (ANCOVA) (General Linear Model, GLM), adjusting for baseline characteristics and measures. Bonferroni correction will be performed for pair-wise comparisons. Linear mixed models will be used to compare the outcomes across time points among the three arms, adjusting for baseline characteristics and measures. Additionally, a priori sensitivity analysis will be conducted for complete cases, i.e. participants with complete follow-up and data. There are no formal planned interim analyses of the primary outcome, but progress reports on all data issues will be presented to investigators of the study team. The level of statistical significance will be set at 0.05 (two-tailed) and 95% confidence intervals will be calculated.

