**Methods:**

This three-arm randomised controlled trial will recruit up to 750 pregnant women from the KK Women’s and Children’s Hospital, Singapore. Participants will be randomly assigned to receive: (1) standard routine care; (2) behavioural nudges (text messages) along with the use of a social media platform; or (3) midwife-led continuity care involving individualised teleconferencing sessions, during pregnancy and post-delivery. Using web-based questionnaires, participants will be assessed for baseline socio-demography and health status in the first visit, with follow-up assessments in the third trimester, at birth, 6-week (primary end-point), 6-, 12-, 18- and 24-month post-delivery. The primary outcome is PSE. Secondary outcomes include health and birth experience, mental wellness, feeding practice, maternal and child nutritional status. Intention-to-treat and per-protocol analyses will be performed using general linear models to test the effects of interventions across three arms. Recruitment has begun in June 2020 and is estimated to complete in September 2022.

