**Medical records retrieval**								
Obstetric and delivery outcomes			√					

*From the International Consortium for Health Outcomes Measurement (ICHOM) Standard Set of Outcome Measures for Pregnancy and Childbirth

*PROMIS* Patient-Reported Outcomes Measurement Information System, *TOPSE* Tool to measure Parenting Self-Efficacy

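### Breastfeeding success is a three-category secondary outcome, but the only outcome models the protocol states are linear models for means

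*Protocol article*

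**What the plan says.** The Statistical analysis section gives one method for comparing arms at a visit: "Differences in outcomes across three arms at each time-point will be compared using the one-way analysis of covariance (ANCOVA) (General Linear Model, GLM"), adjusted for baseline. For comparisons over time it says "Linear mixed models will be used to compare the outcomes across time points among the three arms". Neither sentence is limited to the primary outcome, to scale scores or to continuous measures. The abstract's Methods paragraph agrees: "Intention-to-treat and per-protocol analyses will be performed using general linear models to test the effects of interventions across three arms".

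Methods for categorical data do appear in the same section. Chi-square and Fisher's exact tests, with ANOVA, "will be used to compare differences in baseline characteristics among the three arms". No such method is named for any outcome.

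Under Secondary outcomes, "Secondary outcomes include health and birth experience, mental wellness and nutritional outcomes". Within the nutritional outcomes, "Breastfeeding success is measured according to feeding mode in the past 7 days". There are three response options: breast milk alone, a mixture with formula and/or water, and no breast milk. No numeric score is attached to them. Table 1 schedules this item at birth, 6 weeks and 6 months.

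**The concern.** ANCOVA and linear mixed models need a numeric response. To follow the stated plan for breastfeeding success, the analyst would have to assign numbers to the three feeding modes and compare mean scores. The protocol gives no basis for the spacing between the numbers, and the result depends on that spacing. A mean score also does not answer the natural question, which is how many more mothers in each intervention arm feed only breast milk.

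Two things are at stake. A real change in exclusive breastfeeding could be hidden or diluted. And if the mismatch is noticed only at analysis, the choice of score, dichotomy or test would be made after the data are in hand.

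**Working it through.** The protocol gives no expected feeding-mode proportions and no power figure for this outcome, so there is no stated figure to reproduce. All proportions below are assumptions chosen for illustration, in the order breast milk alone / mixed / no breast milk.

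**1. A mean score can hide a difference.** Score the categories 1, 2, 3.
- Control 40/40/20%: 0.4×1 + 0.4×2 + 0.2×3 = 1.8
- Intervention 50/20/30%: 0.5×1 + 0.2×2 + 0.3×3 = 1.8

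The difference in means is 0, while feeding with breast milk alone differs by 50 − 40 = 10 percentage points.

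The variances differ as well:
- Control: (0.4×1 + 0.4×4 + 0.2×9) − 1.8² = 3.80 − 3.24 = 0.56
- Intervention: (0.5×1 + 0.2×4 + 0.3×9) − 1.8² = 4.00 − 3.24 = 0.76

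**2. The answer depends on the spacing of the score.** The proportions are the same, and a lower score means more breastfeeding.

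| Scores | Control mean | Intervention mean | Reading |
|---|---|---|---|
| 1, 2, 3 | 1.8 | 1.8 | no difference |
| 1, 2, 4 | 0.4 + 0.8 + 0.8 = 2.0 | 0.5 + 0.4 + 1.2 = 2.1 | intervention worse |
| 1, 3, 4 | 0.4 + 1.2 + 0.8 = 2.4 | 0.5 + 0.6 + 1.2 = 2.3 | intervention better |

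All three scorings respect the order of the categories, yet the sign of the effect changes.

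**3. How often does it matter?** A simulation (3,000 runs per scenario) took three arms, two at 30/50/20% and one changed. It compared the one-way ANOVA F-test on scores 2, 1, 0 with the 4-df chi-square test, both at 5% and without covariates. The sizes per arm are 150 (the evaluable number in the Sample size section), 250 (the recruitment target) and 85 (250 × 0.34, what remains if the stated 66% dropout applies in full).

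| Changed arm | Mean score, changed vs other arms | ANOVA / chi-square rejections, n = 85 | n = 150 | n = 250 |
|---|---|---|---|---|
| A: 40/30/30% | 1.10 vs 1.10 | 5% / 69% | 5% / 93% | 5% / 100% |
| B: 40/40/20% | 1.20 vs 1.10 | 15% / 23% | 22% / 42% | 34% / 65% |
| C: 40/45/15% | 1.25 vs 1.10 | 28% / 21% | 46% / 38% | 70% / 62% |

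In A the mean score is blind to the change. In B, mothers move only from mixed feeding to breast milk alone, and the mean score loses roughly half the power at 150 per arm. In C every category moves in the same direction, and the mean score does slightly better. With no effect (40/40/20% in all arms), both tests rejected in 4% to 5% of runs.

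**4. Which categorical model?** A proportional-odds model fitted to the proportions in step 1 gives a common odds ratio of 1.07 in favour of breastfeeding (0.93 in the other direction). The closely related rank-sum test rejects in about 6% to 7% of simulated two-arm comparisons at 150 per arm. That model would therefore miss the same pattern. A logistic comparison of breast milk alone versus other targets the 10-point difference directly, though with limited power: SE = √[(0.4×0.6 + 0.5×0.5)/150] = 0.057, z = 0.10/0.057 = 1.75, and power ≈ Φ(1.75 − 1.96) ≈ 42%.

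**The case against.** The strongest reply is that this is a condensed article. The model for each secondary variable is usually set in the analysis plan, and one general sentence should not be read as the full specification. The authors name chi-square and Fisher tests for baseline data, so they plainly distinguish categorical from continuous variables. A loosely worded summary is at least as likely as an intention to average feeding categories. This stands in part: the protocol nowhere says that feeding mode will be scored 1-2-3, and an unseen plan may already name a suitable model. It does not remove the point, because the article does more than stay silent. It states a method without exception, in two places, and that method does not fit a listed outcome.

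The second reply is that the illustration in step 1 is built so that the means cancel: it needs the intervention to raise both exclusive breastfeeding and no-breast-milk feeding. That is true. It shows what can happen, not what is likely, and scenario C shows a pattern where the linear model loses nothing.

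A reader might go further and call the linear analysis invalid. The simulation does not support that: rejection under no effect stays near 5%. What remains is interpretability, dependence on the score, and lost power for some patterns.

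A reader might also extend the point to the delivery outcomes. Table 1 lists "Obstetric and delivery outcomes" only as an item retrieved from medical records. The article gives no scale for them and does not include them among the primary or secondary outcomes. That they are categorical, or that they would be analysed by ANCOVA, is not documented.

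**Conclusion.** The point holds for breastfeeding success. As written, the protocol assigns a three-category secondary outcome, measured at three visits, to models for means. Followed literally, this requires an arbitrary score, gives no estimate of the proportion feeding only breast milk, and under the assumed proportions ranges from total loss of power (5% versus 93% at 150 per arm) to a slight gain (46% versus 38%). The true cost cannot be sized, because the documents give no feeding-mode proportions.

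It would be wrong to infer that the trial's main result is at risk. For TOPSE, "Participants will be requested to rate items using a 11-point Likert scale ranging from 0 (completely disagree) to 10 (completely agree"), over 48 items, and PSOC has 17 items scored 1 to 6. Summed scores of this kind suit ANCOVA and linear mixed models, and the sample size rests on overall TOPSE. The matter is worth correcting because it is cheap and best settled before results are seen, but it concerns one secondary outcome.

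**What to change.** In the Statistical analysis section, limit ANCOVA and linear mixed models to scale scores and continuous measures. Add that breastfeeding success will be analysed at each visit by logistic regression for breast milk alone versus other, adjusted for baseline characteristics and reported as a risk difference or odds ratio with 95% confidence interval. Add a multinomial model for the three categories, and GEE or mixed logistic models across birth, 6 weeks and 6 months. Align the abstract's wording. If the analysis plan already does this, only the published wording needs to change.

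The cost is one sentence and a little more analysis work in routine software. Data collection, sample size and the primary analysis do not change. The binary comparison discards the distinction between mixed feeding and no breast milk, which the multinomial model restores.
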